#### Inclusion Criteria

2.3.1

Participants will be included in the study if they meet the following conditions: (1) willingness to participate in the study, (2) successful completion of the theoretical course on professional ethics, (3) at least 1 year of clinical experience as a nursing student (internship or externship), and (4) access to and ability to use a smartphone and the internet.

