#### Exclusion Criteria

2.3.2

Participants will be excluded or withdrawn from the study if they: (1) have been diagnosed with psychological or cognitive disorders, (2) have previously participated in similar ethical empowerment workshops, and (3) fail to attend one of the scheduled ethics workshops in the program.

Information regarding psychological or cognitive disorders will be obtained solely through voluntary self‐reporting by participants during the eligibility screening process. No medical records will be accessed, and responses will be kept strictly confidential by the researcher in accordance with ethical approval protocols.

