### Data Collection

2.6

In this study, data will be collected using two questionnaires: a demographic information questionnaire and the Professional Moral Courage questionnaire by Sekerka et al. [14]. The demographic information of the students will be gathered through a written questionnaire at the beginning of the study. Data on the dependent variable (Professional Moral Courage) will be collected immediately before the workshop, immediately after the workshop, 1 month later, and 3 months after the intervention. Both the intervention and control groups will be assessed for this variable, and they will complete the standardized Professional Moral Courage questionnaire by Sekerka et al. [14] in person using printed paper and pencil.

To prevent information leakage and sample contamination, the control group will complete the study first, followed by the intervention group.

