### Sample Size

2.7

The sample size for this study was calculated using G*Power software (version 3.1.9.4), based on the standard formula for comparing means between two independent groups:

$$n={\left(Z(\alpha /2)\right)+Z_{\beta })}^{2}\cdot \left(\sigma_{1}^{2}+\sigma_{2}^{2}\right)/\Delta^{2}.$$

The calculation was informed by the findings of a previous study conducted by Hosseini Yazdan Abad Sofla et al. [31], which reported an effect size of 1.18. Using a significance level of 0.05 and a statistical power of 0.95, the required sample size was estimated at 40 participants. To account for an anticipated 20% attrition rate, the sample size was increased to 48 participants, ensuring adequate power to detect the expected effect even with potential dropouts.

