### Data Management

2.11

The demographic questionnaire will be completed by both the control and intervention groups after obtaining written consent. The intervention and control groups will be assessed on the dependent variable (Professional Moral Courage) immediately before the training workshop, immediately after its completion, 1 month later, and 3 months after the intervention. The standardized Professional Moral Courage Questionnaire by Sekerka et al. [14] will be completed in person and printed format. To minimize and prevent data loss, students will be encouraged and monitored to complete the questionnaires fully at each stage. Additionally, the outcome assessor will receive training to ensure the accurate and complete collection of data. Data entry into SPSS version 26 will be performed by a trained researcher, and the accuracy of the entered data will be verified by another member of the research team. To maintain participant confidentiality, the data will be stored using anonymous code numbers. Finally, data analysis will be conducted by an epidemiologist.

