It is anticipated that scenario‐based ethical education will enhance the professional moral courage of nursing students. Through this approach, students will be able to face ethical challenges in simulated scenarios and make informed decisions that boost their confidence and moral courage in professional environments. The goal of this intervention is to demonstrate that scenario‐based training positively impacts students' ethical competencies and strengthens their moral courage in real‐life situations.

Although the training program addresses multiple educational dimensions, moral courage was selected as the primary outcome due to its integrative nature and strong connection to ethical performance in clinical practice. It reflects not only knowledge and attitudes but also the readiness to act ethically under pressure, which makes it a suitable and measurable indicator of overall ethical development.

Like any other study, this study is not without limitations. Despite efforts to minimize them, certain constraints may exist. One limitation is the inability to conduct in‐person follow‐ups. Consequently, student follow‐ups and reinforcement of educational content were carried out online and remotely. While this virtual follow‐up method may restrict close interactions and direct observation of students' progress, it facilitates continuous access to education and sustained learning. Additionally, due to the nature of the intervention, the study will not be blinded to participants. This could potentially influence the results, although outcome assessors and the epidemiology consultant will remain blinded.

This study assumes that scenario‐based training can improve nursing students' professional moral courage. If the findings of this study are positive, this educational approach could serve as an effective tool for fostering nursing students' moral courage in Iran and other countries, ultimately leading to enhanced professional performance and ethical competencies in real‐life situations.

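### The only outcome is collected in person on paper at all four time points, with no stated route for a student who cannot attend at 1 or 3 months

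*Protocol article*

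**What the plan says.** All references are to the protocol article.

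- **Mode.** Section 2.6 has both groups fill in the questionnaire "in person using printed paper and pencil". Section 2.11 says again that it "will be completed in person and printed format". Neither section offers another mode.
- **Times.** Section 2.6 sets four assessments: "immediately before the workshop, immediately after the workshop, 1 month later, and 3 months after the intervention". Section 2.5 lists no other outcome.
- **Remote access.** Inclusion criterion (4) in 2.3.1 requires "access to and ability to use a smartphone and the internet", and it applies to both classes. In the intervention class the three months of teaching follow-up run through WhatsApp (2.4.2).
- **Retention.** Section 2.11 says that "students will be encouraged and monitored to complete the questionnaires fully at each stage" and that the outcome assessor is trained in complete collection.
- **Attrition.** Section 2.7 raises the sample from 40 to 48: "To account for an anticipated 20% attrition rate". No split by class is given.
- **Withdrawal.** Section 2.3.2 excludes or withdraws participants who "fail to attend one of the scheduled ethics workshops in the program". Only the intervention class has workshops.
- **Order.** Section 2.6 has the control class finish the study before the intervention class starts.

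**The concern.** The mode of collection is a stated rule, given twice, and not a detail on which the article is silent. Read as written, a student who is reachable and willing, but not present at 1 or 3 months, has no stated way to give the only outcome. Encouragement, monitoring and assessor training help with students who are in the room; they do not reach those who are not.

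The plan expects to lose a fifth of its students and responds by recruiting more. That restores numbers. It does not restore comparability if the students who are absent differ in moral courage from those who attend. The methods named in 2.12 (paired t-test and ANCOVA) in their standard form use only students who have the follow-up score being analysed, so a missed sitting removes the student from that comparison. How missing scores will be handled may be set out in the analysis plan and is not raised here. The point is that some of this loss can be avoided at the collection stage, with equipment every participant must already have.

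**Working it through.** **1. The plan's own sample size.** Inputs from 2.7: standardised effect 1.18, alpha 0.05 (two-sided, since the formula uses Z at alpha/2), power 0.95. The exact two-sample t-test gives 20 per group, 40 in total, with power 0.953. The stated 40 is reproduced. The stated 48 is 40 × 1.2. Dividing by the retained fraction would give 40 / 0.8 = 50, a small difference.

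**2. Does loss threaten power?** The class sizes are not stated; 24 and 24 is assumed. Power at an effect of 1.18, two-sided 0.05:

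| Control / intervention observed | Power |
|---|---|
| 24 / 24 | 0.979 |
| 19 / 19 | 0.943 |
| 24 / 16 | 0.945 |
| 24 / 12 | 0.900 |

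A loss of 20% of 48 is 9.6 students, leaving 38.4, or about 19 per class. Even with a third of one class missing, power is 0.945. At the planned effect, power is not the issue.

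**3. Does loss threaten the estimate?** In one class let m be the fraction missing and g the observed mean minus the missing mean, in SD units. The full-class mean is (1 − m) × observed mean + m × missing mean. Hence

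observed mean − full-class mean = m × g,

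and the between-class contrast shifts by

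m(intervention) × g(intervention) − m(control) × g(control).

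The documents give neither m by class nor g, so the following are assumptions:

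- **20% missing in one class, none in the other, g = 0.5 to 1.0.** Shift 0.20 × 0.5 = 0.10 SD to 0.20 × 1.0 = 0.20 SD. Against 1.18 this is 0.10 / 1.18 = 8.5% to 0.20 / 1.18 = 16.9%. It corresponds to 0.20 × 24 = 4.8, about 5 students, and not to the 9.6 that the plan expects.
- **All 9.6 expected losses in one class of 24.** m = 9.6 / 24 = 40%, and the shift is 0.20 to 0.40 SD.
- **20% missing in both classes with the same g.** 0.20 × g − 0.20 × g = 0. The shift cancels.

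The range therefore runs from nothing to 0.40 SD, depending on quantities the documents do not supply. Adding students changes neither m nor g, so the increase to 48 leaves the shift where it was.

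**4. What the text says about imbalance.** Two features could raise loss in the intervention class: only that class can be withdrawn for a missed workshop (2.3.2), and it is assessed later in the calendar (2.6). A third points the other way: that class gives its phone numbers and has weekly contact with the team for three months (2.4.1, 2.4.2), while no contact with the control class between assessments is described.

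**The case against.** Supervised completion on paper is a legitimate mode, and nothing here contradicts itself. Participants are enrolled students at one school, so most can be found. The article does not say that there is a single sitting or that a later in-person sitting is barred, and catch-up arrangements are often left to a full protocol. All of this stands, and it keeps the point small. It does not remove it, because the article names one mode twice and a later sitting still requires the student to come in.

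Three stronger readings are tempting and are not supported.

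- A reader might infer that loss will be larger in the intervention class and so favour the training. No statement or figure says so, and weekly contact could improve retention there. Stopping the WhatsApp activity is also not the same as being absent from school.
- A reader might take the Discussion sentence "One limitation is the inability to conduct in‐person follow‐ups" as an admission that outcome visits cannot be held in person. The sentence that follows shows that it concerns educational follow-up, so it does not conflict with 2.6.
- A reader might treat 0.10 to 0.20 SD as the expected cost of paper collection. It is an illustration: the planned 20% is not attributed to the mode of collection, and the gap between missing and observed students is assumed.

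It is also fair to object that an online form alone would miss students withdrawn for a missed workshop, and that repeating the analysis on paper responses only would drop the same absentees again. Both objections stand, and the fix allows for them.

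**Conclusion.** The point holds as an inexpensive improvement to the design, not as an error. The protocol fixes the only outcome as in-person paper completion at every time point, states no route for absentees, expects 20% attrition, and answers it only with sample size. That protects power (0.943 with about 19 per class, assuming equal classes and the planned effect of 1.18) but gives no protection against selective loss. The size of any bias is unknown. Under an assumed loss of 20% in one class only and an assumed gap of 0.5 to 1.0 SD, it would be 0.10 to 0.20 SD; with equal and similarly selective loss in both classes it would cancel. Direction cannot be settled from the documents, so unequal loss should be described as a risk and no more.

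**What to change.** - **2.6 and 2.11.** Keep in-person paper as the default. Add that any allocated student in either class who is absent at an assessment, and has not withdrawn consent for questionnaires, is sent the same 15 items by a coded online form within a fixed window. Send it individually, not through the intervention class's WhatsApp group.
- **2.3.2.** State that a student who misses a workshop is still asked for all outcome questionnaires. Without this, a change to 2.6 and 2.11 alone would leave those students without outcome data.
- **Reporting.** Record the mode of each response and report its frequency by class. The main comparison uses all responses. A repeat on paper responses only is descriptive, because a difference between the two results could come from mode or from selection.

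Cost: a short amendment and one online form, with no extra participants. The downside is a possible small mode effect for a few students, who would also complete the form outside the monitored setting.

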### Sample Size

2.7

The sample size for this study was calculated using G*Power software (version 3.1.9.4), based on the standard formula for comparing means between two independent groups:

$$n={\left(Z(\alpha /2)\right)+Z_{\beta })}^{2}\cdot \left(\sigma_{1}^{2}+\sigma_{2}^{2}\right)/\Delta^{2}.$$

The calculation was informed by the findings of a previous study conducted by Hosseini Yazdan Abad Sofla et al. [31], which reported an effect size of 1.18. Using a significance level of 0.05 and a statistical power of 0.95, the required sample size was estimated at 40 participants. To account for an anticipated 20% attrition rate, the sample size was increased to 48 participants, ensuring adequate power to detect the expected effect even with potential dropouts.

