### Recruitment

2.8

To conduct this study, the researcher will first obtain permission from the Joint Ethical Committee of the School of Nursing and Midwifery and the School of Rehabilitation at Tehran University of Medical Sciences, as well as permission from the Dean of the School of Nursing and Midwifery. The researcher will then visit the School of Nursing and Midwifery to select samples based on the inclusion criteria. All undergraduate nursing students from 6th semester, which includes two classes, will be considered for the study. Eligible participants will be selected through a census. A list of students will be obtained from the school administration, and students will be invited to participate by the principal investigator during an in‐person meeting. After explaining the study's aims and methods, informed consent will be obtained from all participants. The classes will be randomly assigned to either the intervention group (Class A) or the control group (Class B) using simple randomization. In this phase, further explanations about the study will be provided, and students will be encouraged to follow the study's timeline. To minimize the risk of contamination between the classes and prevent information leakage between the two groups, the control group will be included in the study first, followed by the intervention group.

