### Random Allocation

2.9

The allocation of classes to the intervention or control group will be done using simple randomization, specifically through a coin flip. One class will be assigned to the “heads” side, and the other to the “tails” side. After flipping the coin, the classes will be assigned to either the intervention group (Class A) or the control group (Class B).

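### The 0.95 power for 40 students assumes independent students, but two whole classes are allocated, one per arm, so the power claim holds only if there is no class effect

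*Protocol article*

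**What the plan says.** Section 2.7 (Sample Size) says that the calculation was made in G*Power, "based on the standard formula for comparing means between two independent groups", and takes its effect from an earlier study "which reported an effect size of 1.18". The result is: "Using a significance level of 0.05 and a statistical power of 0.95, the required sample size was estimated at 40 participants". The section then says "To account for an anticipated 20% attrition rate, the sample size was increased to 48 participants" and ends by asserting that this keeps power adequate for the expected effect if students drop out. It mentions neither an intraclass correlation nor a design effect.

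Section 2.8 (Recruitment) says that the sixth semester consists of two classes and that "Eligible participants will be selected through a census". Section 2.9 (Random Allocation) says: "The allocation of classes to the intervention or control group will be done using simple randomization, specifically through a coin flip". Each arm is therefore one class. Section 2.12 (Statistical Analysis) plans t-tests, chi-square tests and ANCOVA at student level and mentions no class effect.

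**The concern.** The sample size section and the allocation sections describe different designs. The formula in section 2.7 treats every student as an independent unit. Under sections 2.8 and 2.9 the unit that receives a treatment by chance is the class, and there are two of them. Students in one class share teachers, placements and discussions, so their scores may be correlated. Any such correlation adds a component to the variance of the difference between arms that recruiting more students into the same class does not reduce.

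Two things are at stake. A null result would be read against a power that the design may not have. A positive result from a student-level test would be read against a 5% error rate that the test does not keep if there is a class effect.

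A smaller slip sits in the same sentence: the allowance for attrition multiplies 40 by 1.2 instead of dividing it by 0.8.

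**Working it through.** **Inputs.** From section 2.7: effect size d = 1.18, taken as a standardised difference because no SD or raw difference is given; alpha 0.05, two-sided because the printed formula uses the alpha/2 quantile; power 0.95; 40 students, raised to 48 for 20% attrition. From sections 2.8 and 2.9: two classes, one per arm. Assumed here: equal class sizes, because none are given, and ICC values of 0.01, 0.05 and 0.10, because none is given.

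**1. The plan's own figure.**
- Printed normal formula: n per arm = 2 × ((1.960 + 1.645)/1.18)² = 18.67, so 19 per arm.
- Noncentral t: power is 0.943 at 19 per arm and 0.953 at 20 per arm. The smallest size reaching 0.95 is 20 per arm, or 40 in total.

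The stated 40 is reproduced for independent students.

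**2. Attrition.**
- 40 × 1.2 = 48, whereas 40/0.8 = 50.
- 48 × 0.8 = 38.4, so about 38 complete (19 per arm). Power is then 0.943 by the t-test and 0.953 by the printed normal formula.
- The loss that leaves 40 of 48 is 8/48 = 16.7%.

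**3. Power with a class effect.** Take total variance 1, m completers per class and one class per arm. The design effect is DE = 1 + (m − 1) × ICC, the standard error of the difference between arms is SE = √(2 × DE/m), and power = Φ(d/SE − 1.960), with the ICC treated as known. For m = 20:

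| ICC (assumed) | DE | SE | d/SE | Power |
|---|---|---|---|---|
| 0 | 1.00 | 0.316 | 3.731 | 0.962 |
| 0.01 | 1.19 | 0.345 | 3.421 | 0.928 |
| 0.05 | 1.95 | 0.442 | 2.672 | 0.762 |
| 0.10 | 2.90 | 0.539 | 2.191 | 0.591 |

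The first row is 0.962 rather than 0.953 because this table uses the normal approximation, so it slightly flatters every row. If all 48 complete (m = 24), power at the three non-zero ICCs is 0.958, 0.796 and 0.614.

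**4. Limit for very large classes.** As m grows, SE tends to √(2 × ICC). Reaching 0.95 needs 1.18/√(2 × ICC) ≥ 3.605, so ICC ≤ (1.18/3.605)²/2 = 0.054. Above that value no class size reaches 0.95, even with the ICC known.

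**5. Type I error of a student-level t-test that ignores class.** The test uses the SD within classes, whose variance is 1 − ICC, while the true variance of the difference is 2 × DE/m. The true SE therefore exceeds the assumed one by r = √(DE/(1 − ICC)), and the actual error is P(|t₃₈| > 2.024/r).
- ICC 0.01: r = 1.096, error 0.073.
- ICC 0.05: r = 1.433, error 0.166.
- ICC 0.10: r = 1.795, error 0.266.

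A simulation of 200,000 trials per value gave 0.074, 0.164 and 0.267. A cruder normal approximation that uses the total SD, 2 × (1 − Φ(1.960/√DE)), gives 0.07, 0.16 and 0.25.

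**6. Class-level analysis.** Two classes minus two arm means leaves 0 degrees of freedom. The ICC between classes cannot be estimated, and a class effect cannot be told apart from the intervention effect. The powers in step 3 are therefore upper figures that no analysis in section 2.12 can deliver.

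**The case against.** The strongest reply is that the size of the loss rests on an ICC that appears nowhere in the article. At ICC 0.01 power is still 0.93 with 20 completers per class and 0.958 with 24. This stands: the article does not show that power is below 0.95, only that 0.95 depends on an unstated assumption. It also stands that a table of powers with a known ICC must not replace the 0.95 as if it were attained power.

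A reader might infer three stronger points that the text does not support.
- *That the article claims power 0.95 with 48 students.* It ties 0.95 to 40 and claims only adequacy for 48. Without loss or class effect, 24 per arm gives 0.979.
- *That the attrition slip leaves the trial underpowered.* It costs two students and about one percentage point of power (0.953 to 0.943), and the printed normal formula is still met at 19 per arm. ANCOVA could recover the difference: if the baseline score is a covariate, which is not stated, an assumed baseline-outcome correlation of 0.2 gives 0.951. Baseline adjustment would not, however, remove class effects that arise during the study.
- *That the census fixes N at 48, so the calculation is idle.* No class sizes are given, eligibility and consent reduce the census, and a census is compatible with checking that the available number is sufficient.

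**Conclusion.** The concern holds as a conditional statement. The 40 is correct arithmetic for independent students, but independence is a property that allocation by class does not provide. The 0.95, and the adequacy claimed from it for 48, hold only at ICC = 0.

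Over the assumed range of 0.01 to 0.10, with 20 completers per class and equal class sizes, power is at most about 0.93 falling to 0.59, and the type I error of a student-level test is about 0.07 rising to 0.27. Both results rest on the assumed ICC and on d = 1.18 being a standardised difference. The confounding of class with treatment rests on neither: it follows from having one class per arm, and no number of students removes it.

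The attrition figure is a minor correction that would not justify a finding by itself.

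**What to change.** Amend section 2.7 as follows:

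1. State that power 0.95 for 40 students assumes no class effect (ICC = 0).
2. Give the powers at ICC 0.01, 0.05 and 0.10 only as an illustrative sensitivity range. Say that the ICC values are assumed, that the figures are optimistic because they treat the ICC as known, and that the planned analysis does not deliver them.
3. Delete the closing clause that claims adequate power in spite of dropouts.
4. State that, with one class per arm, the class effect cannot be separated from the intervention effect, and that the trial's conclusion will be qualified accordingly.
5. Restate the tolerated loss as 16.7% for 48 students.

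This is a change of text only. No further enrolment is needed, and adding students to the same two classes would not solve the main problem. The cost is a less favourable power statement and a more guarded conclusion.
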